## Background

The Centers for Disease Control and Prevention (CDC) state that the coronavirus disease 2019 (COVID-19) caused by SARS-CoV-2, is thought to spread mainly between people who are in close contact with one another within about 6 feet (1.8 m) when an infected person coughs, sneezes or talks. Aerosol droplets containing the SARS-CoV-2 virus have been shown to remain suspended in air for ~3h. These droplets can land in the mouths or noses of people who are nearby or possibly be inhaled into the lungs. It is important to discuss minimal infectious dose and viral load exposure. The minimal infective dose is defined as the lowest number of viral particles that cause an infection in 50% of individuals, The human infectious dose of SARS-CoV-2 remains unknown, but animal studies are a plausible surrogate. Currently, there is no approved vaccine for the prevention of COVID-19 and medications are limited for treatment. In an attempt to decrease viral load exposure, the government initiated a stay at home order to help avoid transmission of COVID-19, but this could result in physical deconditioning if individuals become progressively more sedentary.

This is a new disease and there is limited information regarding risk factors for severe disease. Based on what we know now, the CDC classifies those at high-risk for severe illness from COVID-19 are people 65 years and older, BMI  $\geq 40$ , diabetes, live in nursing home or long-term care facility, chronic lung disease, moderate asthma, heart conditions, or immunocompromised (cancer, organ transplant, HIV, smoking, prolonged corticosteroids, dialysis, liver disease.) It is important to utilize exercise as medicine during this time, not only as an effective way to treat obesity, diabetes, or heart and lung disease that are considered to place a patient at high risk, but also utilizing exercise to precondition individuals prior to developing COVID-19. It is important to consider the significant decrease in cardiorespiratory fitness (CRF) and profound loss of muscle mass when patients are hospitalized for weeks at a time, especially if mechanical ventilation is required. After fighting for their life against COVID-19, at the time of discharge patients will have an ongoing battle to regain the CRF and strength that they lost during the illness. Hence, it is now even more important than ever to prophylactically increase CRF, muscular strength, and optimize body composition through exercise preconditioning.

The use of face masks have also been shown to be effective in decreasing transmission. A randomized controlled trial of 446 nurses comparing the use of surgical masks with the N95 respirator in

protecting health care workers against influenza found that use of a surgical mask compared with an N95 respirator resulted in noninferior rates of laboratory confirmed influenza. In an observational study, researchers assessing the effect of community-wide mask usage to control COVID-19 observed 11 COVID-19 clusters in recreational "mask-off" settings compared to only 3 in workplace "mask-on" settings. Concluding that mask wearing may contribute to the control of COVID-19 by reducing the amount of emission of infected saliva and respiratory droplets from individuals with subclinical or mild COVID-19.

The presence of gaps between the mask and the facial contours will result in air leakage around the mask (face seal leakage) reducing the effectiveness of the mask. Researchers assessing the efficiencies of protection offered to by N95 respirator and surgical masks in 25 subjects to evaluate the 2 pathways of aerosol particle penetration (filter vs face seal) into respiratory protection devices (RPDs). They concluded health care environments should be increasingly focused on the peripheral design rather than on the further improvement of the filter media. The face seal leakage was found to represent the main pathway for the submicrometer particles penetrating into the mask. Thus, concluding that the priority in product development should be given to establishing a better fit that would minimize the face seal leakage to increase protection for the individual wearing the mask. In addition to being effective at decreasing the spread of the virus, a mask must be comfortable enough to be tolerated by the wearer to maximize compliance.

Konda et.al tested the performance of over 15 natural and synthetic fabrics to determine the best materials to use when making a cloth mask. They found that cotton sheets with high thread counts provide the best mechanical protection. However, other materials such as natural silk, chiffon weave or flannel can likely provide good electrostatic filtering of particles. Combining layers to form hybrid masks, leveraging mechanical and electrostatic filtering may be an effective approach. This could include high thread count cotton combined with two layers of natural silk or chiffon, for instance. A quilt consisting of two layers of cotton sandwiching a cotton–polyester batting also worked well. In all of these cases, the filtration efficiency was >80% for <300 nm and >90% for >300 nm sized particles. More importantly they also found that face seal leakage around the mask area can degrade efficiencies > 60%.

Following the severe acute respiratory syndrome (SARS) outbreak that occurred in March 2003, a study by Li et.al. was conducted to investigate the effects of wearing N95 and surgical facemasks by assessing the subjective perception of discomfort and heart rate response to each mask following a walking protocol. Subject completed 3 walking intervals as follows: 20 min at 2.0 mph (3.2 km/h), 10 min at 3.0 mph (4.8 km/h), 10 min at 4.0 mph (6.4 km/h) and resting 10 min between each interval. Subjects rated ten sensations of discomfort: humidity, heat, breathing resistance, itchiness, tightness, saltiness, feeling unfit, odor, fatigue, and overall discomfort, and asked to reply to the question “How do you like the facemask?” by rating on a scale ranging from 0 to 10, with 0 representing “not at all”, 5 representing “acceptable” and 10 representing “very fond of”. In general, the ratings for humidity, heat, breath resistance and overall discomfort increased gradually with time and increase of workload. Surgical facemasks had significantly lower ratings than the N95 facemask, which suggested that when wearing either of the surgical facemasks the subject felt drier, cooler, more able to breathe easily and less uncomfortable than when wearing either of the N95 facemasks. The pattern of changes in mean heart rate amongst these facemasks is similar, reaching peaks at the end of the third exercise session. The subjects had lower mean heart rates when wearing surgical masks than when wearing N95 facemasks. High breathing resistance made it difficult for the subject to breathe and take in sufficient oxygen.

## Significance

The CDC currently recommends that everyone wear a cloth face covering (not surgical masks or N-95 respirators) in public, especially in places where maintaining social distancing is difficult to maintain (e.g., grocery stores and pharmacies). These recommendations become increasingly important as the country gradually begins to lift restrictions by opening more businesses including gyms and fitness centers. Johns Hopkins released a report, “Public Health Principles for Phased Reopening During COVID-19: Guidance for Governors” outlining how to re-open certain categories of activities including gyms and fitness centers while reducing COVID-19 risk. The report states that regardless of business specific considerations, there are measures that can be taken to mitigate the risk of infection to protect individuals. COVID-19 mitigation measures included the use of nonmedical cloth masks, incorporating engineering controls such as physical barriers where possible, and reconfiguring space to enable people to be located at least 6 feet apart. The report

also ranks certain activities by their contact intensity, number of contacts, and the potential to modify them to reduce risk. Identifying gyms and fitness studios as “nonessential” businesses, rating contact intensity, number of contacts, and modification potential all as medium. The purpose of a cloth mask is not to protect the individual wearing the mask, as much as it is to protect other people surrounding them by reducing the viral load shedding into the environment. If individuals are able to exercise at home or outside while practicing appropriate social distancing, then it is reasonable to not wear a mask. However, the COVID-19 pandemic can make it challenging to maintain a physically active lifestyle, and has created concern about exercising as gyms begin to open back up for business. Wearing a mask during exercise is going to impede the ease of breathing. Although decreased facesal leakage results in improved protection, it increases airflow resistance and impede the ease of breathing, which becomes increasingly important during exercise. This highlights the importance of assessing the risk vs benefits of the mask and finding the best mask for that specific exerciser. For high risk individuals it might be more beneficial to protect their self by wearing mask with minimal facesal leakage. However, a mask with slightly more facesal leakage might be more appropriate for individuals that are asymptomatic and exercising at a higher intensity. The CDC recommendation to wear a cloth face covering is to protect people around the individual wearing mask more than individual, which highlights the importance of everyone wearing a mask to protect the community. Especially during times of increased viral shedding including talking, coughing, sneezing, or increased ventilation during physical activity.

This study intends to find out how a cloth mask may impact exercise capacity, to provide guidance for exercisers to adjust their expectations and training accordingly. We plan to assess exercise capacity through estimated peak oxygen consumption ( $\dot{V}O_{2peak}$ ), oxygen saturation and level of perceived exertion during treadmill based exercise while wearing a cloth mask compared to exercising without a cloth mask. The potential significance of this study is to determine if subjects can exercise safely and if their exercise training needs to be adjusted while following the current recommendations of wearing a cloth mask in public. The degree of airflow limitation experienced will depend on the type and fit of the mask being worn, and inadequate airflow could possibly result in CO2 re-breathing if all air was not fully discharged from the mask with each breath. This re-breathing of CO2 could potentially limit the workload leading to a detriment in performance, and increase in

adverse symptoms such as dizziness, lightheadedness, chest pain or shortness of breath that does not improve with rest. Getting used to the mask may be difficult. Practice first with walking. Patients should be reminded not to panic if they are struggling with breathing with the mask on they should just lift up the mask for some extra air taking deep diaphragmatic breaths, and avoiding shallow breathing which can lead to hyperventilation. If we are going to recommend that individuals exercise with cloth masks, it is imperative that future research is conducted to evaluate the degree to which airflow can be limited during exercise by wearing a cloth mask. At the completion of our study, we will have further understanding of the effects of face masks during treadmill based running. To our knowledge this is the first study to assess the effects of wearing protective cloth mask on exercise capacity.

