## EXPERIMENTAL DESIGN & METHODS

**Subject Recruitment:** We will recruit 20 subjects through the Cleveland Clinic. Inclusion Criteria: Healthy subjects age  $\geq 18$ , Exclusion Criteria: Any long-term disease that would interfere with their ability to exercise safely, fever  $\geq 100.4$  F, or pregnancy. Informed consent will be obtained by the CoPI, and need for medical clearance determined based on ACSM's 2015 preparticipation guidelines. (See appendix 12.6) To remain compliant with enterprise guidelines we will not be recruiting healthy subjects outside of the Cleveland Clinic staff at this time to avoid increase COVID-19 exposure risk. However, if the enterprise changes the guidelines we will expand our enrollment to include non Cleveland Clinic employees. Employees will not be solicited by

direct initiation. Recruitment will involve only posted notice or general advertising that does not pressure employees into participating for fear of job loss, delayed promotion, or other influences from their superior.

**Study Design:** The study design is a prospective crossover non-inferiority trial where subjects will complete 3 separate graded exercise treadmill tests each time wearing either No Mask, N-95 Mask (3M), or Cloth Mask (Boco). The order of the mask worn will be randomly assign to minimize familiarization or training effect. All testing will be performed in a Cleveland Clinic facility following standardized COVID-19 screening precautions. We will compare the data collected from each test to asses for differences between subject comfort, peak exercise capacity (eMET), heart rate response during exercise and recovery.

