**Testing:** After completing the informed consent and being medically cleared, subjects will then perform a symptom limited graded exercise treadmill test using a modified Balke protocol. The modified Balke, which is a well-accepted treadmill protocol that keeps the speed constant and increases workload by grade. Subjects will rest for 3 minutes and resting heart rate, blood pressure, subjective perceptions of the face mask will be measured. Subjects then will walk at 0% grade at 3 miles per hour for 2 minutes. Elevation will be increased by 2% after the initial 2 minutes and by 1% each minute thereafter until the test is terminated. Heart rate will be monitor by Polar H10 heart rate monitor and oxygen saturation will be measured with a pulse oximeter. We will continue to monitor heart rate during recovery at 1, 3 and 5 minutes post exercise. We will monitor each stage for perceived exertion, feelings of light headedness, anxiety, and discomfort. The test will also be terminated at the request of the subject or if any chest pain develops. The scale of measuring subjective perceptions instrument will be adminstereted after collecting 5 minutes of resting, end of the exercise test, and at 5 minutes post recovery. The graded exercise test will be performed once with No Mask, once with 3M 8200 N-95 Respirator, and once with a Cloth Mask (Boco). Subjects will be randomized by a random number generater (1= No Mask, 2= N-95, 3= Cloth Mask) to determine the order the perform each exercise test No Mask, N-95 or Cloth Mask and will complete the other tests 2 atleast 1 day apart. Subjects will be instructed to abstain from exercise for 2 days before the test.

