**COVID-19 Precautions**

**Subject**

Temperature screening upon entering building to determine specific temp before denying subject access (100.4). COVID screening questions upon entry in to hospital. Questions to include whether subject has come from a household with a COVID + family/friend. Pending COVID test – deny entry until negative result determined. Sanitizers available per current placement on walls all patient areas. (Deemed adequate by HH IP department already). Subjects instructed on procedure for hand sanitizing. Subjects to wear cloth mask/hospital-provided mask upon entry and exit. Advised use during exercise as tolerated. Instruction on mask donning and doffing done prior to class start. Absolutely no visitors. Subjects to be dropped off so as to limit number of people in department. Subjects 6 feet apart. Testing restricted to 39 minutes to accommodate equipment sanitation, education, flow of people entering and leaving. Should subjects use towels, they must be provided by hospital, used solely by subject and disposed of in appropriate hamper by subject. Directional flow signage to/from waiting area-gym-conference room. Subjects to be provided individual baggies with supply of masks. Monitors are assigned to each subject, sanitized before and after subject use.

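### The test is a graded walk at a constant 3 mph, so the statement about running is unsupported, and peak eMET has an unstated ceiling that, if subjects reach it, favours non-inferiority

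*Protocol*

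**What the plan says.** The Significance section of the protocol closes by promising that "we will have further understanding of the effects of face masks during treadmill based running". The same section describes the assessment more broadly, as treadmill exercise.

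The Testing paragraph of Experimental Design & Methods sets the workload. "Subjects then will walk at 0% grade at 3 miles per hour for 2 minutes", under a protocol that "keeps the speed constant and increases workload by grade". The schedule is: "Elevation will be increased by 2% after the initial 2 minutes and by 1% each minute thereafter until the test is terminated". The test is called symptom limited, and the other stated reasons for ending it are these: "The test will also be terminated at the request of the subject or if any chest pain develops". No maximum grade, treadmill model or equation for eMET is given, and nothing says how to score a subject who reaches the top of the incline range.

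Subject Recruitment admits healthy adults. Apart from fever and pregnancy, the exclusion is "Any long-term disease that would interfere with their ability to exercise safely". There is no upper limit on fitness and no expected capacity. The COVID-19 precautions for subjects add a time limit: "Testing restricted to 39 minutes to accommodate equipment sanitation, education, flow of people entering and leaving".

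The Hypothesis and Statistical Analysis sections make peak exercise capacity the non-inferiority endpoint, with a margin of 1 eMET (3.5 mL/kg/min).

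**The concern.** There are two linked consequences of fixing the speed.

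First, the scope. A walking result would be presented as a result about running. The Significance section intends the study as guidance for exercisers, and the Project Timeline aims at publication before gyms reopen, so the wording could reach readers who run.

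Second, the endpoint. With speed fixed, the largest eMET that can be recorded is set by the machine. A subject whose capacity exceeds that value both with and without a mask gets the same score twice, whatever the mask did. A subject who is stopped by the machine only in the unmasked test shows a smaller loss than the true one. In a superiority trial this would be conservative. In a non-inferiority trial it pushes towards the conclusion the trial hopes to reach.

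**Working it through.** **Scope.** Testing has subjects walk at 3 mph, holds speed constant and changes only grade. No step has anyone run. The running sentence in Significance therefore describes something the design does not test. It is one sentence and does not recur in the Hypothesis, Specific Aims or Statistical Analysis.

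**Where the ceiling lies.** The plan gives no figure here to reproduce. I assume the standard walking equation, VO2 = 3.5 + 0.1·S + 1.8·S·G, with S in m/min and G as a fraction.

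- S = 3 × 26.8 = 80.4 m/min.
- 15% grade: 3.5 + 8.04 + 1.8 × 80.4 × 0.15 = 33.2 mL/kg/min; divided by 3.5 this is 9.5 eMET.
- 20%: 40.5 mL/kg/min, or 11.6 eMET.
- 25%: 47.7 mL/kg/min, or 13.6 eMET.
- One 1% stage: 1.8 × 80.4 × 0.01 = 1.447 mL/kg/min = 0.41 eMET. The margin is 3.5 / 1.447 = 2.4 stages.

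The session limit is a second, higher cap. If the 39 minutes include 3 minutes of rest and 5 of recovery, 39 − 3 − 5 = 31 minutes of exercise remain. The grade in percent roughly equals the minute, so that allows about 30% grade, or 15.7 eMET.

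**Direction of the bias.** Let C be the cap, x the true capacity without a mask and y the true capacity with one. The recorded difference is min(y, C) − min(x, C).

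- Both above C: the difference is 0, whatever y − x is.
- Only x above C: the difference is y − C, which is a smaller loss than y − x.
- Neither above C: the difference is correct.

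The reverse case, only y above C, understates a gain; it is uncommon when the mask truly costs capacity.

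**Size.** I simulated 20 pairs, 20,000 trials per setting, on these terms:

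- x is normal with mean 9 to 12 eMET and SD 2 eMET (both assumed).
- The true mask loss is exactly 1 eMET, so non-inferiority is false.
- The SD of the paired difference is √3.5 / 3.5 = 0.53 eMET. This takes the 3.5 in Statistical Analysis as a variance in (mL/kg/min)².
- Scores are continuous and cut at C.
- Non-inferiority is declared when the one-sided 95% t bound lies inside the margin, so the nominal error is 5%.

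| Maximum grade (assumed) | Mean capacity, eMET | Pairs capped in both tests | Mean observed loss, eMET | False non-inferiority |
|---|---|---|---|---|
| 15% | 9 | 23% | 0.71 | 64% |
| 15% | 10 | 40% | 0.53 | 94% |
| 15% | 12 | 77% | 0.18 | 100% |
| 20% | 9 | 4% | 0.94 | 12% |
| 20% | 10 | 11% | 0.86 | 27% |
| 20% | 11 | 22% | 0.72 | 61% |
| 25% | 9 | 0.3% | 0.99 | 6% |
| 25% | 10 | 1% | 0.98 | 7% |
| 25% | 12 | 10% | 0.87 | 26% |

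A repeat with a different random seed gave error rates within about one percentage point. At one-sided 2.5% the pattern is the same: 88.5% for the second row and 3.5% for the eighth.

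**Is leaving out pairs capped in both tests enough?** No. With a 15% limit and mean capacity 9 to 12 eMET, false non-inferiority after that exclusion is still about 13 to 23%, because pairs capped only without a mask remain and are still biased towards 0.

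**The case against.** The strongest reply is that nothing in the documents shows the ceiling binding. The test is symptom limited, grade rises until the test ends, and neither the treadmill's range nor the subjects' fitness is given. With a 25% limit and mean capacity of 9 to 10 eMET the error is 6 to 7% against a nominal 5%, which is negligible. This stands, and it makes the point conditional. A reader might infer that healthy subjects will reach the maximum grade in both conditions; the documents do not support that.

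A reader might also infer that ceiling pairs help non-inferiority twice, by shrinking the mean loss and by shrinking its SD. The second part is generally wrong. Mixing zeros with real losses usually widens the spread: in most of these settings the SD rises from 0.53 to about 0.6, and it falls only when more than half of pairs are capped in both tests. The error comes from the bias in the mean. For the same reason, an observed mean loss inside the margin is not by itself a non-inferiority finding; the confidence bound must lie inside it.

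The running sentence is a wording slip on which no analysis rests. That is fair, and correcting it is editorial.

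Finally, handling of censored scores could be left to an analysis plan that is not shown. The ceiling itself, however, is created by the workload schedule in the protocol, and the reason a test ended has to be written down at the time. A later plan may not be able to recover it.

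**Conclusion.** The point holds in two parts of different strength.

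The scope mismatch is certain: the design tests graded walking at 3 mph and cannot support a statement about running. It is small, because it sits in one sentence outside the hypothesis and aim.

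The ceiling is certain as a mechanism and unknown in frequency. Under the walking equation and the limits assumed above, recordable capacity stops at about 9.5 to 13.6 eMET. If subjects reach that limit, the mean difference is biased towards non-inferiority. With a true loss equal to the margin, the resulting error runs from close to nominal to above 90%, depending on the treadmill limit and the subjects' fitness, neither of which the protocol gives. It should be dealt with before testing, but it does not show that the trial's conclusion would be wrong.

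**What to change.** - In Significance, replace the reference to running with graded uphill treadmill walking at 3 mph.
- In Testing, state the treadmill's maximum grade and the equation that converts the final stage to eMET.
- Add a form field for the reason each test ended, with reaching the maximum grade as one of the options, and report the number of such tests in each mask condition.
- In Statistical Analysis, add a sensitivity analysis that treats those scores as right-censored, for example a censored-normal mixed model with a subject effect that keeps the pairing. Claim non-inferiority only if it also holds there. Do not rely solely on dropping pairs capped in both tests.

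The cost is one reworded sentence, two stated specifications, one form field, one extra analysis and a narrower claim. If no test ends at the maximum grade, the added analysis has no scores to censor and the reported count of zero settles the question.
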